### Adverse effects of the intervention

Adverse events are defined as any sign of pain perceived by the participants due to the training protocol lasting for 2 days or more. In addition, the occurrence of fall or injury to other body parts during training sessions will be considered as adverse effects. Falls are defined as “an unexpected event in which the participants come to rest on the ground, floor, or lower level” [29].

### Sample size

No formal sample size calculation will be performed for this feasibility study. We will follow the sample size recommendations for pilot randomized controlled trials [30], and we aimed to recruit 18 participants for each group (i.e., total sample size of 36) considering a dropout of 20%. This number of participants is deemed adequate to provide sufficient information on key feasibility issues such as recruitment and acceptability of the intervention.

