**Methods/design:**

A single-blind, parallel, randomized, controlled feasibility trial will be conducted with a sample of 32 individuals diagnosed with idiopathic PD. Participants will be allocated into control group (CG) and experimental group (EG). The intervention of the CG will be conventional physical therapy, and the intervention of the EG will be a supervised practice of five Kinect games. Both groups will perform 14 sessions of 1 h each one, twice a week over 7 weeks. Process outcomes will be safety, feasibility, adherence, and acceptability. Safety will be assessed by the proportion of participants who experienced intervention-related adverse events or any serious adverse event during the study period. Feasibility will be assessed through the scores of the games recorded in all training sessions. Adherence will be assessed through the participant’s attendance. Acceptability will be the motivation of the participants regarding the interventions. Clinical outcomes will be (1) postural control, (2) cognitive function, (3) balance, (4) gait, and (5) QoL. Individuals will be assessed pre- and post-interventions and after 30 days by a blinded evaluator.

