### Procedure

Figure 1 outlines the study phases. Participants in both groups will be allocated to an intervention at the ratio of 1:1. The trial will be carried out over a 7-week period.

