### Statistical analysis

The data analysis for the randomized controlled feasibility trial will be undertaken on an intention-to-treat basis. Demographic data will be presented to evaluate baseline comparability of the groups. Descriptive statistics will be used to characterize the groups at baseline and to present feasibility outcomes. Comparisons of the clinical outcomes between CG and EG will be performed to investigate the feasibility of this trial and to calculate estimates for likely effect sizes and 95% confidence intervals. Differences between the two groups will be presented as an unadjusted mean difference for continuous variables with their associated 95% confidence intervals; effect size will be calculated for paired *t*-test and *p* value with an alpha of 0.05, power of 0.8, and 0.5 correlations between baseline, at the end of the trial, and at follow-up. At the end of the study, data collection and statistical code will be publicly available, while maintaining the anonymity of the participants. All data will be analyzed using SPSS software version 22 (SPSS, Chicago, Illinois).

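### The abstract's sample of 32 and the Sample size section's target of 36 disagree, and the stated 20% dropout does not turn one into the other

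*Protocol article*

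**What the plan says.** Two places in the protocol article give a total.

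- **Abstract, Methods/design:** "randomized, controlled feasibility trial will be conducted with a sample of 32 individuals diagnosed with idiopathic PD". The status of the 32 (recruited, randomised or completing) is not given.
- **Methods/design, Sample size:** "we aimed to recruit 18 participants for each group (i.e., total sample size of 36) considering a dropout of 20"%. This section also says "No formal sample size calculation will be performed for this feasibility study" and refers to published recommendations for pilot trials. It gives neither the base number before the dropout allowance nor the number expected to complete.

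Two other statements bear on how the totals are read. The Procedure section fixes the split: "Participants in both groups will be allocated to an intervention at the ratio of 1:1". The Statistical analysis section fixes the analysis principle: "The data analysis for the randomized controlled feasibility trial will be undertaken on an intention-to-treat basis".

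**The concern.** A reader who meets 32 in the abstract and 36 with a 20% allowance in the methods will assume that 36 are enrolled so that 32 finish. If that worked, the two figures would be compatible and only a word of explanation would be lacking. It does not work, so the article carries two totals that cannot both stand alongside the stated dropout.

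This matters more here than a slip in an abstract usually would. The Sample size section rests the adequacy of the trial on this number and names recruitment among the feasibility questions that the trial should answer. Recruitment cannot be judged cleanly against a target given as both 32 and 36, and a final report that matches either figure could look like a change of plan. The Discussion also says that the results will feed the sample size of a larger trial, so a reader needs to know how many participants are expected to supply complete data.

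**Working it through.** **Inputs**

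- Total in the abstract: 32, which is 16 per arm at 1:1 (Abstract; Procedure).
- Total in the Sample size section: 36, which is 18 per arm.
- Dropout: d = 0.20 (Sample size).

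**Step 1. Can the Sample size section stand alone?** The plan shows no derivation, so there is no calculation to reproduce. The usual inflation is n/(1 − d). A base of 14 per arm gives 14/0.8 = 17.5, rounded up to 18 per arm, or 36 in total. So 36 with 20% is coherent from a base that the article does not state. That base is not 16 per arm.

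**Step 2. Take 32 as the number completing, or as the base before the allowance.**

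- Forward from 32: 32/(1 − 0.20) = 40. Per arm, 16/0.8 = 20, again 40 in total.
- Forward with the cruder add-on n × (1 + d): 32 × 1.2 = 38.4, rounded up to 39.
- Backward from 36: 36 × 0.8 = 28.8, or 18 × 0.8 = 14.4 per arm.
- Loss implied by 36 falling to 32: (36 − 32)/36 = 4/36 = 11.1%.
- The same gap as an add-on to 32: 36/32 − 1 = 12.5%.

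No route gives 36 from 32, or 32 from 36, at 20%.

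**Step 3. Take 32 as the number recruited or randomised.** Then 32 (16 per arm) contradicts 36 directly, because the 36 is itself defined as 18 in each group. With 20% loss, 32 × 0.8 = 25.6 would complete.

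**Step 4. Compare the readings.**

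| Meaning of 32 | What it conflicts with | Expected completers |
|---|---|---|
| Completing, with 36 recruited | The 20% (implied loss 11.1%) | 32 |
| Completing, with 20% loss | The 36 (40 would be needed) | 32 |
| Recruited or randomised | The 36 | 25.6 |
| Abstract figure wrong; 36 and 20% stand | Nothing further | 28.8 |

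Under every reading at least one of 32, 36 and 20% has to change.

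**Step 5. Size of the consequence.** The 95% half-width of a standardised difference between arms is t(0.975, 2n − 2) × √(2/n). At n = 18 per arm it is 0.68 SD and at n = 16 it is 0.72 SD. The choice between 36 and 32 alters precision only slightly.

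**The case against.** The strongest reply is that the Sample size section is the governing text, that it states the target explicitly, and that it is coherent by itself (Step 1). On that view there is one stale number in an abstract and nothing in the design is at fault. Most of this stands. The target is contradicted, but it is stated. The reply does not remove the conflict, however: the abstract is part of the same published protocol, and nothing in the text shown says which figure takes precedence. The flow diagram (Fig. 1) is not visible here and may carry a number, so the point is limited to the text available.

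It is also fair to say that little turns on this statistically. The alpha and power in the Statistical analysis section belong to the effect-size calculation ("effect size will be calculated for paired *t*-test and *p* value with an alpha of 0.05, power of 0.8, and 0.5 correlations"), not to the sample size, and Step 5 shows a small difference in precision.

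Three stronger readings are tempting, and the article supports none of them.

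- A reader might infer that the 36 came from 15 per arm × 1.2, so that the sponsor multiplied where division was needed and a target of 30 completers is missed. No base of 15 per arm and no target of 30 appear anywhere, and 14 per arm with the usual division also gives 18.
- A reader might infer that the number of completers is overstated. That follows only if 32 means completers, which the abstract does not say.
- A reader might infer that both totals are wrong. Correcting a single figure is enough to resolve the conflict.

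**Conclusion.** The point holds as an internal contradiction. The article gives totals of 32 and 36, and its own 20% dropout does not connect them, so at least one of the three figures is wrong as written. The discrepancy is 4 participants in the target (2 per arm). If 32 is read as completers, it is 3.2 above the 28.8 that 36 and 20% imply. This rests only on the stated figures, on 1:1 allocation, and on dropout being a proportion of those recruited; the add-on form in Step 2 fails as well. Which figure is wrong cannot be settled from the document. No power or type I error statement is affected. The reason to correct it is that recruitment is one of the things this feasibility trial is meant to assess.

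**What to change.** State one recruitment target in both the abstract and the Sample size section, say that it is the number recruited, and add the number expected to complete.

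- **If 36 and 20% are kept:** replace the abstract's 32 with 36 (18 per group) and state that about 28 to 29 are expected to complete, about 14 per arm.
- **If 36 recruited and 32 completing are meant:** label the abstract's 32 as completers and restate the dropout allowance as about 11%.

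Either change is wording only and enrols nobody extra. The cost is presentational: the first route states fewer completers than a reader of the abstract might have assumed, and the second states a smaller allowance for dropout.

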### Randomization, allocation concealment, and blinding

The participants who fulfill the inclusion criteria will be randomly assigned to one of two groups (experimental or control group) with the same number of participants. Stratified randomization will be achieved by generating a separate block for each stage of PD stages (I, II and III). After all, individuals have been identified and assigned into the blocks, simple randomization will be performed within each block to assign individuals to one of the groups (EG or CG) [31]. Two physical therapists blinded to treatment allocation will record all measurements. The evaluators will be blinded to the type of intervention that individuals will receive. Individuals will be oriented to not comment to the evaluators about any details of the intervention that they will receive.

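### Simple randomisation within each disease stage does not ensure the equal groups the protocol states, and balances stage no better than no stratification

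*Protocol article*

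**What the plan says.** All on this point stands in the protocol article.

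- **Randomization, allocation concealment, and blinding** states the result wanted: participants "will be randomly assigned to one of two groups (experimental or control group) with the same number of participants".
- The same section gives the structure: "Stratified randomization will be achieved by generating a separate block for each stage of PD stages (I, II and III"). One block per stage makes the block a stratum. No block size, allocation rule or minimisation is described.
- On method, it says that "simple randomization will be performed within each block to assign individuals to one of the groups (EG or CG"). On timing, it places this step after participants have been sorted into their stage lists.
- **Procedure** gives the ratio: "Participants in both groups will be allocated to an intervention at the ratio of 1:1".
- **Sample size** gives the target: "we aimed to recruit 18 participants for each group (i.e., total sample size of 36) considering a dropout of 20" per cent. The abstract instead describes a trial "with a sample of 32 individuals diagnosed with idiopathic PD". That discrepancy is a separate matter, so both totals are used below.
- **Statistical analysis** plans group differences as unadjusted mean differences with 95% confidence intervals. Stage does not enter.

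**The concern.** Simple randomisation ordinarily means that each participant is assigned independently, with no constraint on the totals. Doing this separately in each stage list changes nothing: every participant still has an independent 50:50 assignment. Stratification improves balance only when allocation within the stratum is restricted. As written, the plan states an outcome (equal numbers) and a design feature (stratification by stage) that its named method does not deliver.

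Stage is the only factor the plan chose to stratify on, and the stated comparison does not adjust for it. A chance difference in stage between the groups would add avoidable noise to the postural control, gait, cognition and quality-of-life estimates. The Discussion says the results will be used to size a larger multicentre trial, so that noise would carry into the next design.

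**Working it through.** **Inputs.** Total N = 36, 18 per group (Sample size); N = 32 as a sensitivity case (abstract). Three strata, stages I, II and III, with independent assignment at p = 1/2 inside each (Randomization section). The documents give no stage mix, so the stratum sizes in step 3 are assumptions.

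**Step 1: does the stated method give the stated 18:18?** If the stages hold n1, n2 and n3 participants, the experimental group size is Bin(n1, 1/2) + Bin(n2, 1/2) + Bin(n3, 1/2) = Bin(N, 1/2), whatever the stage mix. For N = 36:

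- P(18:18) = C(36,18)/2^36 = 0.132.
- Expected absolute difference = N × C(N, N/2)/2^N = 36 × 0.132 = 4.75. The standard deviation of the signed difference is √36 = 6.
- P(difference of 6 or more, that is 21:15 or worse) = 0.405.
- P(difference of 8 or more, that is 22:14 or worse) = 0.243.

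For N = 32, P(16:16) = 0.140 and P(difference of 6 or more) = 0.377. The choice of total does not alter the picture.

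**Step 2: does stratifying help?** The between-group difference in the share of stage III participants was simulated with and without the stage lists. Its standard deviation was 0.162 both ways for assumed strata of 12/12/12, and 0.149 both ways for 9/18/9. This follows from step 1: the two schemes are the same scheme.

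**Step 3: imbalance within stages.** The probability that a stage is split 2:1 or worse depends on its size:

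- Stage of 12 (8:4 or worse): 2 × (1 + 12 + 66 + 220 + 495)/4096 = 0.388.
- Stage of 6 (4:2 or worse): 1 − 20/64 = 0.688.
- Stage of 18 (12:6 or worse): 62360/262144 = 0.238.
- Stage of 9 (6:3 or worse): 260/512 = 0.508.

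The probability that at least one stage is split this badly is then:

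- 12/12/12: 1 − 0.612³ = 0.77.
- 9/18/9: 1 − 0.492 × 0.762 × 0.492 = 0.82.
- 6/18/12: 1 − 0.3125 × 0.762 × 0.612 = 0.85.

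A more concentrated mix of 6/24/6 gives 0.92. Every stage is balanced to within one participant with probability 0.012, 0.045 and 0.013 for the three listed mixes.

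**Step 4: cost of unequal group sizes alone.** Efficiency relative to equal groups is 4·a·b/N². For 21:15 it is 4 × 21 × 15/1296 = 0.97; for 22:14 it is 0.95. Unequal totals by themselves cost little.

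**Step 5: what restriction would give.** If a random half of each stage list goes to each group, the difference is at most 1 per stage. With an even total at most two stages can be odd, so the overall difference is at most 2, and 0 is attainable. Permuted blocks of 4 within stage limit the difference to 2 per stage. For assumed strata of 6/18/12 they give 18:18 with probability 0.50 and 20:16 at worst; for 12/12/12 they always give 18:18.

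**The case against.** The strongest reply is that the authors meant a restricted draw. The text promises equal numbers and appears to randomise only after participants have been identified and sorted by stage. That fits drawing half of each list at random, with the word simple meaning no further sub-blocking. On that reading the probabilities in steps 1 to 3 of the working do not arise. The intention is plausible, but the text does not say it, the usual meaning of the named method is the opposite, and Table 4 places allocation on Day 1 with enrolment, which leaves the timing unclear. Someone building the list from this wording could properly produce unrestricted allocation.

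The second reply is that little is lost. This is a feasibility trial with no formal sample size calculation. Safety, adherence and acceptability do not depend on 18:18, and step 4 shows about a 3% efficiency loss at 21:15. The worst stage figures come partly from small strata, where 4:2 already counts as 2:1. All of this stands, and it limits the weight of the point.

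Four stronger readings might be inferred, and the document supports none of them:

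- That the method cannot produce equal groups. It can, about 13% of the time; it does not ensure them.
- That the protocol promises stage balance. It states equal group numbers; stage balance is only implied by stratifying.
- That the 1:1 ratio under Procedure is contradicted. Independent assignment at p = 1/2 satisfies a 1:1 allocation ratio.
- That the comparison would be biased. Simple randomisation is unbiased; chance stage imbalance is random error, which the planned confidence intervals already reflect.

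**Conclusion.** The point holds as a mismatch between the stated design and the named method. Read in its ordinary sense, simple randomisation within stage leaves the chance of the stated equal split at 0.13 for N = 36 (0.14 for N = 32) and makes the stratification inert. The group-size figures rest only on independent 50:50 assignment. The stage figures also rest on assumed stage mixes. The consequence is avoidable chance imbalance and some lost precision in the clinical estimates, which the unadjusted comparison does not recover. Validity is not threatened. It should be fixed, and before allocation starts, because balance by design cannot be restored afterwards; it is not a flaw that would stop the trial.

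**What to change.** Replace simple randomisation in the Randomization section with a named restricted method within stage, according to how enrolment will run.

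- **All participants listed before allocation:** assign a random half of each stage list to each group, with the odd participant in a stage allocated at random. The difference is then at most 1 per stage.
- **Rolling enrolment:** use concealed permuted blocks of varying size (2 and 4) within stage, and change the equality statement to approximately equal numbers, since incomplete blocks can leave a small difference.

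In either case, include stage as a factor in the clinical-outcome comparisons, so that the analysis follows the allocation.

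The cost is a sentence or two of text and a regenerated list, with no extra participants or staff. Small blocks are slightly more predictable, which varying their size and concealing the sequence limit. The analysis gains one model term (two degrees of freedom for three stages).

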### Statistical analysis

The data analysis for the randomized controlled feasibility trial will be undertaken on an intention-to-treat basis. Demographic data will be presented to evaluate baseline comparability of the groups. Descriptive statistics will be used to characterize the groups at baseline and to present feasibility outcomes. Comparisons of the clinical outcomes between CG and EG will be performed to investigate the feasibility of this trial and to calculate estimates for likely effect sizes and 95% confidence intervals. Differences between the two groups will be presented as an unadjusted mean difference for continuous variables with their associated 95% confidence intervals; effect size will be calculated for paired *t*-test and *p* value with an alpha of 0.05, power of 0.8, and 0.5 correlations between baseline, at the end of the trial, and at follow-up. At the end of the study, data collection and statistical code will be publicly available, while maintaining the anonymity of the participants. All data will be analyzed using SPSS software version 22 (SPSS, Chicago, Illinois).

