## Discussion

This protocol will clarify whether an intervention based on Kinect games will be feasible, safe, and acceptable for individuals with PD compared to conventional physical therapy. We will verify whether the proposed interventions can improve clinical outcomes as postural control, gait, cognition, and QoL of individuals with PD. Our hypothesis is that both Kinect games and conventional physical therapy will be feasible, safe, and acceptable for individuals with PD and will promote positive clinical effects. The results of this feasibility study will be used to design a future definitive clinical trial.

There is strong evidence of the effectiveness of conventional (or usual) physical therapy to improve the motor and non-motor functions in individuals with PD [9, 12, 13]. However, to our knowledge, this will be the first randomized clinical feasibility trial that will investigate the safety, feasibility, and clinical outcomes of the Kinect games compared to conventional physical therapy in individuals with PD.

Previous studies have shown that interactive video games can improve motor and cognitive functions of individuals with PD [11, 12, 16]. Video games have emerged as a new low-cost virtual reality tool that can be potentially used in rehabilitation. The games can stimulate multi-directional displacements, weight transfer, controlled movements close to stability limits, a high number of repetitions, auditory and visual feedback, attention, planning, decision-making, sustained concentration, promoting motivation, and commitment in the tasks performed [11, 16]. However, commercial video games have not been developed specifically for individuals with neurological disorders, which could hinder their safety and feasibility to this population.

This study protocol is an innovative clinical feasibility trial regarding the evaluation of the feasibility, adherence, safety, acceptability, and effectiveness of the use of the Kinect games in comparison to conventional physical therapy in individuals with PD. The final results will be used to calculate the sample size needed for a potential larger multicenter trial. Our study may contribute to the understanding of the potential benefits of the interactive Kinect video game technology in rehabilitation of individuals with PD.

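### The planned effect size comes from a paired t-test with a preset correlation of 0.5 and a power of 0.8, so it measures change within a person, not EG against CG

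*Protocol article*

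**What the plan says.** All of the analysis text is in the Statistical analysis section of the protocol article.

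- Analysis set: the analysis "will be undertaken on an intention-to-treat basis".
- Purpose: clinical outcomes are compared between CG and EG, among other reasons "to calculate estimates for likely effect sizes and 95% confidence intervals".
- Between-arm estimate: "Differences between the two groups will be presented as an unadjusted mean difference for continuous variables with their associated 95% confidence intervals".
- Effect size, in the same sentence: "effect size will be calculated for paired" t-test. A p value accompanies it.
- Parameters attached to that effect size: "with an alpha of 0.05, power of 0.8, and 0.5 correlations between baseline, at the end of the trial, and at follow-up".

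Other sections bear on this. Trial design and Procedure describe a parallel-group trial with 1:1 allocation. Outcome measures schedules every measurement at baseline, week 7 and 30 days later. Sample size disclaims any formal calculation and aims for 18 per group, allowing for 20% dropout. Randomization stratifies by PD stage (I, II, III). The Discussion expects benefit in both arms, and adds: "The final results will be used to calculate the sample size needed for a potential larger multicenter trial".

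**The concern.** The stated purpose is a contrast of CG with EG, but the effect size is attached to a paired test. EG and CG participants are different people and are not matched, so the only pairs are one person's values at two visits. The resulting effect size is change within an arm. The comparator is active and both arms are expected to gain, so this number may say little about the difference between them.

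The other parts of the clause do not fit an analysis either. The trial measures the correlation between visits, so there is no reason to set it in advance. A power of 0.8 describes a design for a given effect and SD, and the article gives neither.

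What is at stake is the later trial. If the paired effect size is what gets passed on, its sample size would rest on the wrong contrast and an assumed correlation. A smaller, separate matter is that fixing the between-arm difference as unadjusted sets aside the baseline values and the stratification factor.

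**Working it through.** **Inputs.** From the article: 18 per group, correlation 0.5, alpha 0.05, power 0.8. The article gives no target effect, SD or test sidedness. Assumed for illustration: outcome SD = 1, equal at each visit; two-sided 0.05; true baseline-to-post correlation r from 0.3 to 0.8; the effects named below.

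**1. Can the article's power figure be reproduced?** No, because no effect or SD is given. By exact t calculation at 18 per arm, 80% power corresponds to a between-arm difference of 0.96 SD, or to a paired effect of 0.70 within one arm. For a between-arm difference of 0.5 SD, power is about 31%. The 0.8 is therefore not a property of this trial at a moderate effect.

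**2. What fixing r = 0.5 does.** SD of change = SD × √(2(1 − r)). At r = 0.5 this is √1 = 1, so the SD of change is forced to equal the outcome SD. The paired effect size is d / √(2(1 − r)). For a raw gain of 0.5 SD:

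| True r | SD of change | Paired effect size |
|---|---|---|
| 0.3 | 1.18 | 0.42 |
| 0.5 | 1.00 | 0.50 |
| 0.7 | 0.77 | 0.65 |
| 0.8 | 0.63 | 0.79 |

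**3. Within-arm against between-arm.** Normal approximation, n per arm = 2(1.960 + 0.842)² / d² = 15.70 / d², with r = 0.5.

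- EG gains 0.6 SD, CG gains 0.3 SD. The within-EG effect of 0.6 gives 15.70 / 0.36 = 43.6, so 44 per arm. The between-arm effect is 0.6 − 0.3 = 0.3, which gives 15.70 / 0.09 = 174.4, so 175 per arm.
- Both gain 0.5 SD. The within-arm effect gives 15.70 / 0.25 = 62.8, so 63 per arm. The between-arm effect is 0, and no sample size would detect it.

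**4. Why the observed r is worth having.** For a between-arm difference of 0.5 SD, multiply 62.8 by 2(1 − r) for change scores or by 1 − r² for baseline adjustment:

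| r | Change scores, n per arm | Baseline-adjusted, n per arm |
|---|---|---|
| 0.3 | 88 | 58 |
| 0.5 | 63 | 48 |
| 0.7 | 38 | 33 |
| 0.8 | 26 | 23 |

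**5. Precision lost by not adjusting.** The article does not say whether the unadjusted difference is in final values or in change, so both are shown. The standard error of the adjusted estimate, as a ratio, is √(1 − r²) against final values and √((1 + r) / 2) against change.

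- r = 0.5: 0.866 against either, a cut of 13%.
- r = 0.7: 0.714 against final values, a cut of 29%; 0.922 against change, a cut of 8%.

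At 18 per arm, the 95% CI half-width for final values is t(34) × √(2/18) = 0.68 SD. With baseline adjustment (one further degree of freedom) it is 0.59 SD at r = 0.5 and 0.48 SD at r = 0.7.

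**The case against.** The strongest reply is that the plan already contains what is needed. It states a between-arm mean difference with a 95% CI, and randomisation makes that difference unbiased without adjustment. A reader might infer from the paired clause that the plan never estimates EG against CG. The text does not support that, since the fault lies in the effect-size clause alone. Leaving out baseline and stage costs precision but is not an error, and the gain from adjusting is modest if the comparison is already in change scores.

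A reader might also infer that non-completers are dropped despite intention-to-treat, because a paired test needs both values. The article states no exclusion and no missing-data rule, and a condensed article may leave that rule to a fuller document. The point does not hold.

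Third, the Discussion says only that the final results will size the larger trial, not that the paired effect size is the input. This also stands, so the mis-sizing is conditional.

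Finally, the clause might be meant as planning parameters for the later trial. Even so, a paired test does not suit a parallel-group comparison, and a correlation observed in this trial would be a better starting point than an assumed 0.5.

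**Conclusion.** The effect-size clause is wrong as written. It yields a within-person quantity where the stated purpose is a CG-to-EG comparison, presets a correlation that the trial measures, and cites a power with no calculation behind it. The harm to the later trial depends on which figure is carried forward. In the illustration it is 44 against 175 per arm, which rests on assumed gains of 0.6 and 0.3 SD, SD = 1 and r = 0.5, none of them from the article.

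The lack of adjustment is a secondary point about efficiency, not bias. The standard error could fall by 13% at r = 0.5, and at r = 0.7 by 29% or 8% depending on the comparator. The true r is unknown until the data are in.

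**What to change.** Delete the paired t-test effect size, the fixed 0.5 correlation and the power of 0.8 from the Statistical analysis section. In their place, state that:

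- EG minus CG will be estimated at week 7 and at the 30-day follow-up, adjusted for the baseline value of the outcome and for Hoehn and Yahr stage as used in randomisation, with a 95% CI;
- the estimate uses all randomised participants, as allocated, who have at least one post-baseline value;
- the observed SDs and the observed correlations between visits will be reported as inputs for the definitive trial.

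The change is to wording only and needs no new data. It costs a few degrees of freedom for baseline and stage. A participant with no post-baseline value still contributes nothing to this estimate, so the number of such participants should be given by arm.
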